Applying these methodological frameworks to the specific population under study and using a finite population correction formula with a 95% confidence level and –5% to +5% precision margin, a minimum of 178 participants is required from an eligible population of 330 professionals. This calculation ensures both representative coverage of the target population and sufficient variability in usability and acceptability responses across clinical roles (physicians, registered nurses, and nursing assistants). Accounting for an anticipated 20% attrition rate, 223 participants will be invited to take part. This sample size substantially exceeds the minimum thresholds recommended for summative usability evaluation and pilot feasibility studies [27,29,31] and, therefore, is considered appropriate to achieve the dual objectives of this study: generating robust usability and acceptability data and informing the design of a subsequent full-scale evaluation.

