#### Phase 2: Pilot-Testing

A pilot study will be conducted using a convenience sample of health care professionals described in the Study Setting and Participants section to evaluate the usability and feasibility of the chatbot. Following approval from the ethics committee, eligible participants will receive an email invitation detailing the study objectives, procedures, and ethical considerations. Participants who provide informed consent will be granted access to the chatbot.

This phase aims to assess usability, readability, and overall user experience through a mixed methods approach combining quantitative and qualitative data collection. This study follows the SPIRIT (Standard Protocol Items: Recommendations for Interventional Trials) and CONSORT-EHEALTH (Consolidated Standards of Reporting Trials of Electronic and Mobile Health Applications and Online Telehealth) guidelines.

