### Ethical Considerations

The study will be performed in accordance with good clinical practice and the Declaration of Helsinki. This study received approval from the Provincial Ethics Committee of Almería (code: 132/2024). Health care professionals will participate in the study on a voluntary basis and may withdraw at any time without providing justification and without any impact on their legal rights. All participants will receive clear and detailed information regarding the study’s objectives, procedures, and potential implications and must provide informed consent prior to inclusion.

The *Sanidad Segura* chatbot will request explicit consent before collecting, processing, or transmitting any personal data. The information collected will be used exclusively for the purposes described in the study protocol and for the management of aggression in accordance with established institutional procedures.

Participant confidentiality and anonymity will be maintained at all times. Personal data will be processed in compliance with Regulation (EU) 2016/679 of the European Parliament and the Organic Law 3/2018 on the Protection of Personal Data and Guarantee of Digital Rights. For analysis purposes, data will be handled in an anonymized manner so that no participant can be identified.

Safety considerations include escalation pathways to human services in cases of high-risk disclosures.

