## Results

The study has been funded for a 2-year period starting on December 18, 2024. This study will generate both quantitative and qualitative outcomes to evaluate the chatbot. Quantitative outcomes will include usability scores measured using the SUS and readability scores assessed using the Inflesz scale, along with participants’ sociodemographic characteristics.

Data collection was conducted between February and May 2026. A final convenience sample of 105 participants was obtained. At the time of manuscript submission, data analysis had been completed using SPSS Statistics (version 30.0; IBM Corp). The analyses included descriptive statistics, group comparisons, and correlation analyses as part of the pilot study. The results are expected to be published in an open-access journal in September 2026, with a potential second publication derived from the qualitative analysis anticipated in 2027. Qualitative findings will be derived from semistructured interviews, allowing for an in-depth exploration of user experience. Thematic analysis will be used to identify key themes related to usability, user experience, and suggestions for improvement.

Finally, quantitative and qualitative findings will be integrated through a convergent mixed methods approach using triangulation techniques to provide a comprehensive understanding of the usability, acceptability, and readability of the chatbot.

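### The finite-population calculation cannot ensure representative coverage or spread across clinical roles, because participants are a voluntary convenience sample

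*Protocol article*

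**What the plan says.** The sample size is obtained "using a finite population correction formula with a 95% confidence level and –5% to +5% precision margin", which leads to the statement that "a minimum of 178 participants is required from an eligible population of 330 professionals". The next sentence draws the conclusion at issue: "This calculation ensures both representative coverage of the target population and sufficient variability in usability and acceptability responses across clinical roles", naming physicians, registered nurses and nursing assistants. The target is then inflated: "Accounting for an anticipated 20% attrition rate, 223 participants will be invited to take part".

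The recruitment is described elsewhere. Under Phase 2: Pilot-Testing: "A pilot study will be conducted using a convenience sample of health care professionals", and "eligible participants will receive an email invitation detailing the study objectives, procedures, and ethical considerations". Under Ethical Considerations: "Health care professionals will participate in the study on a voluntary basis". Under Results: "A final convenience sample of 105 participants was obtained". The article states no random selection, no role quotas or strata and no weighting. It gives no rule for choosing whom to invite. The Results section neither restates the precision for 105 nor withdraws the claim of representative coverage.

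**The concern.** A finite population correction is a result about random sampling without replacement from a list. It says how far a sample proportion is likely to fall from the proportion in the whole list when chance alone decides who is drawn. Here the staff decide for themselves whether to take part, so the ±5% loses its probability meaning. Nor does the formula contain anything that governs the mix of roles: a sample of 178 could consist largely of one profession and still satisfy it.

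This is a positive statement about what the calculation achieves, and the article's own sampling method defeats it. A separate analysis plan could not make it true. At stake is what the pilot may conclude. The article says that the data will inform a later full-scale evaluation, and it foresees possible extension to other regions. If the claim passes into the results paper, readers may take the usability and acceptability findings as describing emergency and critical care staff in the district, when they describe those who volunteered.

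**Working it through.** **Inputs.** From Study Setting and Participants: N = 330; 95% confidence (z = 1.96); margin e = 0.05; 20% attrition; SUS SD of about 15. From Results: n = 105. The article does not state the proportion p; p = 0.5 is assumed.

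**1. Reproduce the plan's figures.**

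n = N z² p(1−p) / [e²(N−1) + z² p(1−p)]

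z² p(1−p) = 3.8416 × 0.25 = 0.9604

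n = 330 × 0.9604 / (0.0025 × 329 + 0.9604) = 316.93 / 1.7829 = 177.8, rounded up to 178.

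The variant n₀/(1 + n₀/N), with n₀ = 384.15, gives 177.5, also 178. Attrition: 178 / 0.80 = 222.5, rounded up to 223. Both stated figures reproduce, which supports reading the ±5% as the margin for a proportion.

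**2. The same formula at the planned and achieved n, granting random sampling for the moment.**

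Margin = 1.96 × √(0.25/n), multiplied by √[(N−n)/(N−1)] when the correction is used.

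| n | Share of 330 | Without correction | With correction |
|---|---|---|---|
| 178 (planned) | 53.9% | ±7.3 points | ±5.0 points |
| 105 (achieved) | 31.8% | ±9.6 points | ±7.9 points |

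The 105 are 59.0% of the required 178 (105/178).

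**3. Mean SUS at n = 105.** 1.96 × 15/√105 = 29.4/10.247 = ±2.9 points, without the correction.

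**4. Compare what the formula needs with what was done.** The margins in steps 2 and 3 contain sampling error only. The formula needs random selection from the 330; the article describes email invitation followed by voluntary consent. Control of role mix needs strata or quotas; none is stated. So the margins are nominal, and the assurance about coverage and roles has no source at either n.

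**5. How large a difference would use up the ±5 by itself?** This is an illustration; the article gives no such difference. If all 225 non-participants (330 − 105) share one true proportion, the shift is the participant/non-participant difference × 225/330. A difference of 5 × 330/225 = 7.3 points is then enough. If instead exactly 223 were invited, and being invited was unrelated to the answer, self-selection acts on 118 of 223 (223 − 105 = 118). The difference needed is then 5 × 223/118 = 9.4 points. The article does not say how the invited were chosen, so 7.3 to 9.4 points is a range under assumptions, not an estimate.

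**The case against.** The strongest reply is that one sentence of justification is overclaimed and nothing in the analysis depends on it. Statistical Analysis lists descriptive summaries and group comparisons and names no confidence interval, margin or workforce-level estimate. The sample size is said to be guided mainly by usability requirements. The sample is openly called a convenience sample, and the Discussion positions the work as a feasibility and usability study. The 105 obtained also exceed the cited 40 to 100 for summative usability work. Professional category and workplace setting are collected and will be described.

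Much of this stands, and it rules out several stronger readings that a reader might infer:

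- That the plan sets out to report the workforce's SUS score with a quantified margin. No section plans that.
- That selection error is known to exceed sampling error. The article gives no difference between participants and others, and the only SUS-point precision it cites is 5 to 10 points either way.
- That SUS scores are inflated because volunteers are more at ease with digital tools. That is plausible, but the article offers nothing to show it.
- That the design was to sample about a third of staff. That is the achieved share (105/330); the plan was 54% (178/330). The shortfall is a separate matter, since the claim fails at either size.

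What the reply does not rescue is the assurance itself. Calling the sample a convenience sample in one section does not correct a sentence in another that says representative coverage is ensured. Describing the participants is also not the same as comparing them with the 330.

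**Conclusion.** The point holds as a correction to a stated property of the design. The calculation yields a number, 178, correctly; it cannot yield representative coverage or an adequate spread across roles, whatever the n. The ±5% is nominal, and even on its own terms it belongs to the planned sample. The restated margins for 105 are those in the working; they rest on p = 0.5 for a proportion and an SD of 15 for SUS, and cover sampling error alone. The size and direction of any self-selection error cannot be determined from the article.

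The objection is to the claim, not to running the pilot. A convenience sample is acceptable for usability and feasibility work, provided that conclusions stay with the people who volunteered.

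**What to change.** 1. Delete the statement that the calculation ensures coverage and variability across roles.
2. Describe the ±5% as nominal and valid only under random sampling, and restate it for n = 105 with the figures above, giving p = 0.5 and SD = 15 as assumptions.
3. Say beside these margins that they exclude self-selection error, and name voluntary participation as a limitation.
4. Limit conclusions to the volunteers who took part.
5. Where staff counts by professional category are available, tabulate the 105 against the 330 by role. The total of 330 does not by itself show that such counts are held.

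A role-weighted mean SUS is at most an optional sensitivity result. The article reports the quantitative analysis as complete, so it should be labelled post hoc. It would correct role mix only and would not remove bias from digital engagement. Finer weighting by category and unit risks sparse cells with 105 people.

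The cost is a few sentences and, if counts exist, one table; no new participant data are needed. The downside is that the stated precision and generalizability become less favourable.

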### Procedure

#### Phase 1: Chatbot Design, Development, and Content Validation

The design of the chatbot will be guided by a review of the literature, protocols, and guidelines on the prevention and management of aggression. In addition, a multidisciplinary expert panel will be established comprising health care professionals, lawyers, national police officers and civil guards, psychologists, and social workers with experience in aggression cases. The content validity index proposed by Lawshe [33] will be used to evaluate the relevance, comprehensibility, and clarity of each item as assessed by the expert panel. Content validity will include both item-level and scale-level indexes, with an expert panel of 12 members. An average content validity index of 0.8 or higher will be considered indicative of good content validity. Additionally, the modified κ coefficient will be calculated to determine the proportion of agreement regarding item relevance, with values of κ of 0.60 or higher considered acceptable.

During chatbot development, both software engineers and health care professionals will collaborate to ensure that the tool meets users’ needs. The chatbot will be accessible online, maintain confidentiality, and be designed for intuitive use. The chatbot will follow a hybrid rule-based conversational architecture based on predefined decision trees informed by institutional protocols and expert consensus.

Natural language processing techniques will be used to categorize user inputs into predefined intent categories, allowing the chatbot to guide users through structured conversational pathways based on decision tree logic. The chatbot will guide the user through a structured pathway including emotional validation, assessment of immediate needs, provision of coping strategies, and step-by-step instructions for incident reporting. Depending on user input, the system adapts responses within predefined decision trees to ensure consistency and safety.

The development will incorporate an approach centered on empathy and emotional understanding, providing supportive, validating, and nonjudgmental responses directed toward health care professionals. The chatbot will deliver practical information and resources to assist users in managing aggressive situations effectively.

The empathetic approach of the chatbot is operationalized through predefined supportive language patterns, including validation of emotional experiences, normalization of reactions to workplace aggression, and encouragement to seek appropriate support. This empathy is directed exclusively toward the health care professional and does not involve adaptive emotional inference beyond predefined categories.

During this phase, the focus will be on chatbot development and content validation. Technical performance aspects such as system functionality, response consistency, and alignment with institutional protocols will be internally tested by the research team and expert panel to ensure readiness for pilot evaluation. Crisis escalation pathways will be implemented. In cases of high-risk content, the chatbot will provide emergency contact information and recommend immediate human support.

#### Phase 2: Pilot-Testing

A pilot study will be conducted using a convenience sample of health care professionals described in the Study Setting and Participants section to evaluate the usability and feasibility of the chatbot. Following approval from the ethics committee, eligible participants will receive an email invitation detailing the study objectives, procedures, and ethical considerations. Participants who provide informed consent will be granted access to the chatbot.

This phase aims to assess usability, readability, and overall user experience through a mixed methods approach combining quantitative and qualitative data collection. This study follows the SPIRIT (Standard Protocol Items: Recommendations for Interventional Trials) and CONSORT-EHEALTH (Consolidated Standards of Reporting Trials of Electronic and Mobile Health Applications and Online Telehealth) guidelines.

### Quantitative Measures

#### Sociodemographic Variables

Data will be collected on sex, age, workplace setting, professional category, years of professional experience, length of time in the current unit, and prior experience of workplace aggression (current or past violence survivor).

#### Readability Assessment

Chatbot responses will be evaluated using the Inflesz scale [26], a validated instrument for assessing readability in Spanish texts. Scores range from 0 to 100 and are categorized as follows: very difficult (<40), somewhat difficult (40-55), standard (55-65), fairly easy (65-80), and very easy (>80).

#### Usability Assessment

Usability will be measured using the SUS [34,35], a validated 10-item questionnaire assessing perceived usability across dimensions such as learnability, efficiency, and satisfaction. Each item is rated on a 5-point Likert scale. Final scores range from 0 to 100, with higher scores indicating better usability. Scores will be interpreted as follows: poor (<60), marginal (60-69), acceptable (70-79), good (80-89), and excellent (≥90).

### Qualitative Data Collection

Qualitative data will be collected through semistructured interviews conducted after chatbot use focusing on user experience, perceived usefulness, emotional impact, and suggestions for improvement, as well as through open-ended survey responses embedded within the usability questionnaire. To better understand participants’ experiences with the chatbot, the interviews will include open and conversational questions such as “Can you tell me how you felt while using the chatbot?” “Was there any part that you found especially helpful or unhelpful?” “Did the information and responses seem clear to you?” “Did you encounter any difficulties while interacting with the chatbot?” and “What would you change or improve if you could?” An interview guide will be developed to ensure consistency across participants while still allowing for flexibility to explore emerging topics and deepen relevant aspects of the experience. These questions are intended to encourage participants to speak freely about their perceptions of usability and the usefulness of the intervention.

### Qualitative Analysis

A reflexive thematic analysis will be conducted following the methodology of Braun and Clarke [36]. The analysis will proceed through the following phases: (1) data familiarization, (2) initial code generation, (3) theme development, (4) theme review, (5) theme definition and naming, and (6) reporting.

Two independent researchers will code the data inductively. A coding framework will be iteratively developed and refined through regular meetings. Discrepancies will be resolved through discussion and consensus and, if necessary, consultation with a third researcher. Data management and coding will be supported by qualitative analysis software. To enhance rigor, strategies such as investigator triangulation, audit trails, and reflexivity will be used.

### Mixed Methods Integration

A convergent mixed methods design will be used (Figure 1). Quantitative and qualitative data will be collected concurrently, analyzed separately, and then integrated during interpretation.

**Figure 1 figure1:**
[figure not shown]
Mixed methods study design for the development and pilot validation of the Sanidad Segura chatbot for health care professionals exposed to workplace aggression in Almería, Spain. CVI: content validity index; NLP: natural language processing; SUS: System Usability Scale.

Integration will be conducted through triangulation to compare findings across data sources; joint displays to visually integrate quantitative and qualitative results; and examination of convergence, complementarity, and discrepancies.

This approach will provide a comprehensive understanding of chatbot usability, acceptability, and readability, ensuring that quantitative findings are contextualized and enriched by qualitative insights.

### Ethical Considerations

The study will be performed in accordance with good clinical practice and the Declaration of Helsinki. This study received approval from the Provincial Ethics Committee of Almería (code: 132/2024). Health care professionals will participate in the study on a voluntary basis and may withdraw at any time without providing justification and without any impact on their legal rights. All participants will receive clear and detailed information regarding the study’s objectives, procedures, and potential implications and must provide informed consent prior to inclusion.

The *Sanidad Segura* chatbot will request explicit consent before collecting, processing, or transmitting any personal data. The information collected will be used exclusively for the purposes described in the study protocol and for the management of aggression in accordance with established institutional procedures.

Participant confidentiality and anonymity will be maintained at all times. Personal data will be processed in compliance with Regulation (EU) 2016/679 of the European Parliament and the Organic Law 3/2018 on the Protection of Personal Data and Guarantee of Digital Rights. For analysis purposes, data will be handled in an anonymized manner so that no participant can be identified.

Safety considerations include escalation pathways to human services in cases of high-risk disclosures.

### Statistical Analysis

Quantitative data will be analyzed using SPSS (version 30; IBM Corp). A descriptive analysis will be performed for all variables. Continuous variables will be summarized using means and SDs (or medians and IQRs where appropriate), whereas categorical variables will be presented as frequencies and percentages. Normality will be assessed using the Kolmogorov-Smirnov test. Depending on data distribution, parametric tests (Student *t* test and one-way ANOVA) or nonparametric equivalents (Mann-Whitney *U* test and Kruskal-Wallis test) will be applied to compare groups. Associations between categorical variables will be examined using the chi-square test. A significance level of a *P* value of less than .05 will be adopted.

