### Study Setting and Participants

Participants will be recruited from health care professionals currently active in emergency and critical care units in the Almería Health District (Spain). Eligibility will be restricted to individuals engaged in active clinical practice within the designated units. Professionals currently enrolled in any formal structured intervention targeting workplace aggression—whether psychological, legal, or organizational in nature—will be excluded. This criterion is intended to prevent potential confounding between ongoing therapeutic or remedial processes and the experimental chatbot exposure, thereby preserving the internal validity of the usability and acceptability assessments.

Sample size estimation for this pilot study was primarily guided by the requirements of the planned summative usability evaluation rather than by hypothesis testing for clinical efficacy outcomes—an approach consistent with current methodological guidance for pilot and feasibility studies of digital health technologies [27,28]. For summative usability assessments using standardized instruments such as the System Usability Scale (SUS), Sauro and Lewis [29] recommend samples of between 40 and 100 participants to achieve margin-of-error estimates of –5 to 10 points to +5 to 10 points at the 95% confidence level, thereby enabling clinically interpretable and psychometrically reliable scoring. Sample sizes within this range also provide sufficient statistical power to detect moderate between-group differences in SUS scores (ie, ≥5 points assuming an SD of approximately 15) and to generate stable estimates of acceptability and perceived usefulness across professional subgroups [29,30]. For pilot feasibility studies specifically targeting digital health interventions, precedent in the published literature supports the use of samples of 40 to 70 participants to ensure adequate precision in the estimation of key design parameters for future confirmatory trials [27,31,32].

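### A Kolmogorov-Smirnov pretest decides whether groups are compared on mean SUS or on ranks, although the sizing argument is in SUS points; with unequal spreads this can raise false positives

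*Protocol article*

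**What the plan says.** The Statistical Analysis section of the protocol article sets the rule in three steps.

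- **Pretest:** "Normality will be assessed using the Kolmogorov-Smirnov test". The section does not give its level, the variant (with or without the Lilliefors correction for an estimated mean and SD), or whether it is run on pooled or per-group scores.
- **Choice of test:** "Depending on data distribution, parametric tests (Student" opens the sentence naming the t test and one-way ANOVA. The rank alternatives close it: "test and Kruskal-Wallis test) will be applied to compare groups".
- **Decision:** a P "value of less than .05 will be adopted".

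The descriptive plan in the same section reads "Continuous variables will be summarized using means and SDs (or medians and IQRs where appropriate".

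Study Setting and Participants says sizing was guided by the summative usability evaluation "rather than by hypothesis testing for clinical efficacy outcomes". Its supporting argument is in SUS points: margins of error of 5 to 10 points at 95% confidence for 40 to 100 participants, and between-group differences of at least 5 points with an SD of about 15. The Usability Assessment section reads SUS against cut-offs at 60, 70, 80 and 90 points. The Results section reports 105 participants, with analysis complete and group comparisons included.

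**The concern.** A plan should fix the quantity being compared before the data are seen. Here it is fixed afterwards. If the pretest does not reject, the comparison is of mean SUS in points. If it rejects, the comparison is of rank distributions, which gives no difference in points and is not a test of equal means. Two analysts following the same text could report different quantities from the same 105 scores, depending on the variant they select.

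This sits badly with the article's own rationale. Margins of error, a 5-point difference and point bands are all statements about SUS points. A rank P value answers none of them and gives a later full-scale evaluation no difference or SD to plan with.

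The two branches also handle unequal spread poorly. Student t and one-way ANOVA assume equal variances. The rank tests respond to differences in shape and spread as well as location. If the article's three clinical roles differ in size and spread, either branch can give a small P value when mean SUS is the same.

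**Working it through.** **1. The plan's own figure.** With N = 330, precision 0.05, z = 1.96 and p = 0.5 (assumed, not stated):

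n = N z² p(1−p) / [e²(N−1) + z² p(1−p)] = 330 × 0.9604 / (0.8225 + 0.9604) = 316.93 / 1.7829 = 177.8, so 178.

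178 / 0.80 = 222.5, so 223 invited. Both figures reproduce. The formula is a ±5% finite-population calculation and uses neither a mean SUS nor its SD.

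**2. Precision in SUS points** (SD 15 from the article, no finite population correction):

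| Total n | Half-width for mean, 1.96 × 15/√n | Half-width for difference, two equal groups, 1.96 × 15 × √(4/n) |
|---|---|---|
| 178 | ±2.2 | ±4.4 |
| 105 | ±2.9 | ±5.7 |

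**3. How often the pretest switches to ranks.** SUS has 10 items on a 5-point scale, hence 10 × 4 = 40 steps over 100 points, or 2.5 points per step. I simulated beta-shaped scores rounded to that grid, n = 105. The mean of 75 and the shape are assumptions; the SD of 15 is the article's. The 5% critical distances are about 0.087 with the Lilliefors correction and 0.131 without.

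| Assumed mean | Rejects, Lilliefors | Rejects, uncorrected |
|---|---|---|
| 75 | 92–93% | 19–21% |
| 70 | 73% | 7% |
| 80 | over 99% | 60% |

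With near-normal scores of equal SD in two groups, clipped to 0–100 on the same grid, the Lilliefors version rejects in 26–32% at n = 105.

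**4. Rejection of equal means at P<.05.** Same beta-shaped scores, mean 75 in both groups, n = 105. Ranges cover repeated simulations of 4,000 to 6,000 replicates and pooled or per-group pretesting. Group sizes and group SDs are assumptions.

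| Groups | SDs | Two-stage, Lilliefors | Two-stage, uncorrected | Welch, no pretest |
|---|---|---|---|---|
| 20/85 | 20/12 | 15–17% | 14–16% | 6.0–6.5% |
| 52/53 | 18/12 | 9.5–11% | 5–6% | 4.8% |
| 52/53 | 15/15 | 5% | 5% | 5% |
| 20/85 | 15/15 | 5% | 5% | 6% |

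In the first row both branches contribute: Student t alone rejects in 15.5% and Mann-Whitney alone in 16.2%. In the second row Student t alone is at 4.9% and Mann-Whitney at 10.4%, so the excess comes from the changed hypothesis.

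**5. Other shapes and three groups** (Lilliefors pretest, n = 105 and 178):

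- Near-normal, SD 12 v 18, equal groups: 5.0–6.0%.
- Near-normal, 75/25 split with the smaller group more variable: 8.4–9.9%, Welch 4.6–5.6%.
- Skewed near the ceiling (mean 80), SD 12 v 18: 10–24%, Welch 4.5–5.9%.
- Three skewed groups, SD 12/15/18: 12–14%, Welch 5–7%.
- Same distribution in both groups, normal or skewed: 4.1–5.2%.

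**The case against.** Four objections have force.

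- **No inflation from the pretest itself.** When groups share a distribution, the two-stage rule stays near 5%. The excess needs unequal spreads, and the article gives neither group SDs nor group sizes. A rank test that rejects between distributions that really differ is in error only if the hypothesis is equal means, and the Statistical Analysis section does not say so. This stands: a reader might infer that the plan raises false positives, but the documents support only that it can.
- **The mean is not abandoned, and 178 was not derived from it.** Means and SDs are the first-named summary, and 178 comes from the finite-population formula. The SUS precision argument supports that number but does not produce it. So it would be too much to say that the plan discards the quantity it was sized to estimate.
- **Multiplicity.** The Sociodemographic Variables section says "Data will be collected on sex, age, workplace setting, professional category, years of professional experience, length of time in the current unit", plus prior experience of aggression. A reader might count seven tests at .05 and infer a familywise error of 1 − 0.95⁷ = 30%. No section says each variable is tested, and age, experience and time in unit are unlikely to be independent. That figure is not supported.
- **A condensed article need not spell out intervals.** True. The absence of an interval is not a finding here. The point is the mismatch between a stated selection rule and a stated rationale in SUS points.

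The article also calls this a feasibility and usability study, and no decision in it hangs on a subgroup P value. That limits the consequence. It does not settle which quantity is compared.

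**Conclusion.** The point holds in a limited form. The article states a data-driven rule that leaves open whether groups are compared on mean SUS or on ranks. The outcome depends heavily on an unstated detail: about 92% of samples switch with the Lilliefors correction and 19% to 21% without, for assumed skewed scores at n = 105. The rule can reject equal means in about 10% to 16% of samples when spreads differ (SD 12 against 18 to 20, assumed), against about 5% for Welch. With near-equal group sizes that excess largely disappears under the uncorrected pretest, and with equal SDs it disappears altogether. Welch stayed between about 4% and 7% throughout, so it loses little when the pretest would have been harmless. This is worth changing because the better method is simple, but it does not show that any result already obtained is false.

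**What to change.** Replace the selection rule in the Statistical Analysis section as follows.

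- Drop the Kolmogorov-Smirnov pretest.
- Report mean SUS with a 95% CI and read both limits against the bands in the Usability Assessment section. At n = 105 and SD 15, a mean within 2.9 points of a cut-off cannot be assigned to one band with confidence.
- Compare two groups by the Welch mean difference with 95% CI, and three or more by Welch ANOVA, whatever the shape of the scores. Give medians and IQRs as description.
- Label all group comparisons exploratory.

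The work is one rewritten paragraph and a rerun of standard SPSS procedures on data in hand. Since the Results section says analysis is complete, the change has to be disclosed as made after analysis, with the tests planned in the article reported alongside and the Kolmogorov-Smirnov variant actually used stated. Some subgroup statements now called significant may be lost.
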